## Data collection and management

### Plans for assessment and collection of outcomes {18a}

Clinical data, including patient admission information, demographic data, laboratory blood examinations, and imaging examinations, will be collected from the electronic medical record (EMR). The CRFs will be initially filled out on paper and then entered into Microsoft Excel by the associated researchers. The follow-up period will last for 90 days, during which the researchers will record all medical data and laboratory results from any hospital visits. At the end of the follow-up period, the patients will be interviewed via telephone.

### Plans to promote participant retention and complete follow-up {18b}

Telephone follow-up will be systematically conducted to prompt patients to attend follow-up appointments at 30 and 90 days post-surgery. Additionally, the trial will offer patients financial assistance, encompassing travel expenses and accommodations.

### Data management {19}

Patient data will be initially sourced from the Electronic Medical Record (EMR) and subsequently transcribed onto the Case Report Form (CRF). The patient data will be securely stored in Excel format on a computer. The CRF will meticulously capture specific details of adverse events (AEs) experienced by the patients.

To ensure the quality of trial data, we employ data range checks. Prior to the commencement of the trial, expected ranges for each measurement variable are established, grounded in prior research, clinical guidelines, or professional consensus. These ranges are designed to be both reasonable and aligned with clinical practice. Pre-data entry, range checks are executed to eliminate potential human errors. Post data entry, the utilization of graphical tools and visualization methods such as histograms and box plots aids in identifying outliers or issues with data distribution. We also have dedicated data monitors who randomly inspect the CRFs completed by study personnel. Any identified outliers will be promptly documented and reported.

### Confidentiality {27}

The original Case Report Forms (CRFs) and Informed Consent Forms (ICFs) will be securely stored in a locked filing cabinet within the Department of Cardio-Thoracic Surgery at Nanjing Drum Tower Hospital, The Affiliated Hospital of Nanjing University Medical School. Only data monitors possess the authorization to access and review the hard-copy documents within the filing cabinet. Patient identification details will not be disclosed in any publications. Following the publication of the article, trial data will be shared with other researchers through secure electronic means, such as email, to facilitate international prospective meta-analyses.

### Plans for collection, laboratory evaluation, and storage of biological specimens for genetic or molecular analysis in this trial/future use {33}

All patients will provide aortic dissection tissue samples during surgery, which will be sent to the laboratory for hematoxylin–eosin staining, western blot, and immunofluorescence. Additionally, blood samples will be collected before surgery and at 1, 3, 5, and 7 days after surgery. These blood samples will also be sent to the laboratory for ELISA. The tissue specimens will be stored at room temperature after being embedded in paraffin or frozen in liquid nitrogen and stored in a refrigerator at − 80 ℃. Similarly, the blood samples will be centrifuged and stored in a refrigerator at − 80 ℃.

## Statistical methods

### Statistical methods for primary and secondary outcomes {20a}

Statistical analysis will be performed using SPSS software (version 26.0) and R (× 64 3.5.0). Continuous variables will be presented as mean ± standard deviation. The Kolmogorov–Smirnov test will assess normal distribution. If variables exhibit normal distribution, an independent sample *t*-test will be employed; otherwise, the Mann–Whitney *U* test will be utilized. Categorical variables’ frequency will be expressed as percentages and analyzed using the chi-square test or Fisher’s exact test. It should be noted that we are not conducting an Intention to Treat analysis due to the exclusion of patients with more than 10% missing data. Double-tailed *p*-values and 95% confidence intervals will be reported, with statistical significance defined as *p* < 0.05.

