#### Secondary endpoints

Erythrocyte sedimentation rate (ESR), C-reactive protein, procalcitonin, SII [17], coagulation function (prothrombin time, activated partial prothrombin time, bleeding time), liver function (alanine transaminase, glutamic transaminase, lactate dehydrogenase, total bilirubin, direct bilirubin), renal function (creatinine, uric acid, eGFR), high-sensitivity troponin T, serum B-type natriuretic peptide, myocardial enzyme (creatine kinase, creatine kinase MB isoenzyme), and other laboratory examination of blood;Chest X-ray (for pulmonary inflammation and effusion, etc.), CTA scan of the cervical, thoracic, and abdominal aorta artery (for aortic diameter and extent of dissection, etc.), cardiac ultrasound (for cardiac ejection fraction and left ventricular diastolic dysfunction, etc.), and other imaging examinations.The patient’s cardiopulmonary bypass time during surgery, total surgical time, aortic cross-clamping time, and postoperative hospital stay;Postoperative drainage color, drainage volume, postoperative patient blood transfusion, and transfusion volume;The incidence of postoperative sternal infection, secondary debridement, secondary tracheal intubation, pneumonia, and delirium; andEnzyme-linked immunosorbent assay (ELISA) will be performed to detect and measure IL-1β IL-2, IL-4, IL-6, IL-8, IL-10, IL-12, IL-13, TNF-α, INF-γ, granulocyte–macrophage colony-stimulating factor (GM-CSF) and calcitonin;

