### Sample size {14}

The required sample size was calculated using the PASS (15.0.5) software. The primary endpoint of efficacy was used to calculate the sample size. In the literature, the total death rate of hospitalization after surgery was 25% [7], the incidence of organ malperfusion syndrome was 15–33% [19, 20], permanent dialysis was 2.6% [21], tracheotomy was 8% [22], neurological impairment was 6.9% [22], postoperative mechanical circulatory support was 20% [23], unplanned cardiac reoperation was 4.2% [24], and postoperative cardiac arrest was 0.7–5.2% [25]. Therefore, we assumed that the incidence of composite endpoint events in the control group is 70%, and the incidence of composite endpoint events in the ketorolac group is reduced to 40%. Using PASS (15.0.5) software, when the sample size of the ketorolac group and the control group is 53 cases, this difference can be detected with over 90% confidence. Considering that the loss of follow-up rate is higher than 10%, the final total sample size of this experiment is 120 cases, with 60 cases in the experimental group and 60 cases in the control group.

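### Continuous variables are all to be shown as mean ± SD, even those that the plan's own normality check sends to the Mann–Whitney test (minor; continuous secondary endpoints only)

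*Protocol article*

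**What the plan says.** All of the relevant rules stand in one paragraph of the protocol article, Statistical methods for primary and secondary outcomes {20a}:

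- Summary: "Continuous variables will be presented as mean ± standard deviation". No condition is attached.
- Check: "The Kolmogorov–Smirnov test will assess normal distribution".
- Test: an independent-samples t-test if the variable is normal; "otherwise, the Mann–Whitney *U* test will be utilized".
- Inference: two-sided p-values "and 95% confidence intervals will be reported". Neither the quantity nor the method of the interval is named.

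No median, interquartile range, transformation or rank-based estimate appears anywhere in the article.

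The variables concerned are listed under Secondary endpoints. They begin with "Erythrocyte sedimentation rate (ESR), C-reactive protein, procalcitonin, SII" and continue through liver, renal and cardiac markers, a cytokine panel, drainage and transfusion volumes, and operating times including "aortic cross-clamping time, and postoperative hospital stay". The Discussion names IL-6, CRP and PCT as the markers that ketorolac might lower. The components under Primary endpoint are events, not measurements.

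**The concern.** The choice of test depends on the normality check, but the choice of summary does not. Once the plan has judged a variable non-normal, it compares ranks and still prints two moments that a few extreme patients can dominate. The reader then sees a description and a p-value that answer different questions.

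The Mann–Whitney branch may well be used often. The listed markers, volumes and durations cannot be negative, and many are plausibly right-skewed. They include the three markers on which the Discussion rests its expected benefit.

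The interval raises a second, conditional question. The mean is the only measure of location named, so an analyst could reasonably attach a confidence interval for a difference in means to a Mann–Whitney p-value. The two can then point in different directions.

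**Working it through.** **The article's own figure.** The only calculated figure is the sample size for the binary composite, 70% against 40% (Sample size {14}). With unpooled variance, two-sided 5% and 90% power:

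n = (1.960 + 1.282)² × (0.70×0.30 + 0.40×0.60) / 0.30² = 10.51 × 0.45 / 0.09 = 52.5, so 53 per arm.

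Allowing 11% loss, 53 / 0.89 = 59.6, so 60 per arm. The figure reproduces. It does not bear on this point, except that 53 is used below as the number analysed per arm.

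**Assumptions.** The article gives no SD, distribution or expected effect for any continuous variable. Log-normal values with log-SD s from 0.5 to 1.25 are assumed, with the median set to 1.

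**Step 1: what the summary shows.** Mean = exp(s²/2); SD = mean × √(exp(s²) − 1); quartiles = exp(±0.6745 s).

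| s | mean ± SD | median (IQR) |
|---|---|---|
| 0.5 | 1.13 ± 0.60 | 1.00 (0.71–1.40) |
| 0.75 | 1.32 ± 1.15 | 1.00 (0.60–1.66) |
| 1.0 | 1.65 ± 2.16 | 1.00 (0.51–1.96) |
| 1.25 | 2.18 ± 4.24 | 1.00 (0.43–2.32) |

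The SD equals the mean when exp(s²) − 1 = 1, that is at s = √(ln 2) = 0.83. Above that, mean minus SD is negative for a quantity that cannot be.

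**Step 2: how often such a variable reaches Mann–Whitney.** With 60 simulated values, a Kolmogorov–Smirnov test with plugged-in mean and SD and no correction rejects normality in 17% of samples at s = 0.5, 68% at 0.8, 92% at 1.0 and 98% at 1.2. With the Lilliefors correction the rates are 73%, 99%, nearly 100% and 100%. The article does not say which version is meant.

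**Step 3: the interval, if it is for a mean difference.** Trials were simulated with 53 per arm and a true ratio of 0.6. The Mann–Whitney result was compared with the Welch 95% interval for the difference in means. The share of Mann–Whitney-significant results whose interval includes zero was:

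| s | share of significant results |
|---|---|
| 0.5 | about 0.2% (3,000 trials; 0.1% in a run of 20,000) |
| 0.75 | 9% |
| 1.0 | 29% |
| 1.25 | 47% (48% in repeat runs) |

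The denominator matters. At s = 1.0 the 29% is a share of significant results; as a share of all simulated trials it is about 21%.

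**The case against.** The strongest reply is that this is table style. No test, p-value, error rate, analysis set or sample size changes, and the primary composite is binary. An SD larger than the mean is not an error: it tells an alert reader that the data are skewed. A mean is also a legitimate summary for totals such as drainage volume, transfused volume or days in hospital. This stands as an argument about severity. It does not remove the mismatch, because the article states an unconditional rule that fits badly with its own next two sentences. That is different from leaving a detail to the analysis plan.

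A reader might infer more than the article supports, in two ways:

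- That the plan commits itself to intervals which contradict its p-values. It does not. The interval clause names no quantity and closes a paragraph that also covers categorical outcomes. A mean difference is only an inference from the one summary named, and leaving the interval method to a fuller document is ordinary for an article.
- That the Mann–Whitney route offers no interval except one for means. That is wrong. The Hodges–Lehmann interval comes from inverting that very test, and the software named in the article can produce it.

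The size is also wholly assumed. At log-SD 0.5 the interval conflict almost vanishes, and a ratio other than 0.6 would give other figures.

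**Conclusion.** The point holds as a minor fault in a stated rule: mean ± SD is prescribed for variables that the plan itself will have judged non-normal and tested on ranks. This part needs no assumption about the intervals. How misleading the summary would be depends on the skewness. Under log-normality with log-SD 0.5 to 1.25, the mean overstates the median by 13% to 118%.

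The conflict between interval and p-value is conditional on three things: intervals for mean differences, log-normal data and a true ratio of 0.6. Under those conditions it affects from about 0.2% to 47% of significant results, which is too wide a range for any single figure to be quoted as the expected rate. Only continuous secondary endpoints are touched.

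**What to change.** In Statistical methods for primary and secondary outcomes {20a}, make the summary follow the test:

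- Variables analysed by t-test: keep mean ± SD, and give the mean difference with its 95% interval.
- Variables analysed by Mann–Whitney: give median (IQR) and the Hodges–Lehmann shift with its 95% interval.
- For every interval, name the quantity it describes.

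For positive biomarkers, a log-scale analysis with a geometric mean ratio and 95% interval is an alternative. It replaces the test as well as the summary, so it would have to be fixed before any unblinded comparison.

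The main change costs a sentence or two and a different table layout. It needs no further patients or data, leaves the sample size and the planned p-values as they are, and uses the software already named. Trial status reports 55 of the 120 patients included on 20 March 2024, so the wording could be settled while recruitment continues.

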### Intervention description {11a}

The surgeries will be performed by [name]. The study will commence on the day the patients sign an informed consent form and receive their randomized numbers. The ketorolac group, consisting of patients with aTAAD, will be treated with ketorolac. They will receive a preoperative intramuscular injection of 60 mg per 2 ml ketorolac and a postoperative injection of 30 mg per 1 ml ketorolac BID for two consecutive days. The placebo group, also consisting of patients with aTAAD, will receive placebo treatment. They will receive a preoperative intramuscular injection of 2 ml 0.9% saline placebo and a postoperative injection of 1 ml 0.9% saline placebo BID for two consecutive days. During the administration of ketorolac, patients’ blood pressure and renal function will be routinely monitored, and targeted treatment methods such as sedation, hypotension, diuresis, and dialysis will be applied as necessary. Additionally, all included patients will receive the same medical and surgical treatments in accordance with the diagnosis and treatment guidelines for aTAAD. Aortic dissection tissue samples will be collected for laboratory study during the surgery. Both the ketorolac group and the placebo group patients will undergo follow-up examinations before surgery and on the 1st, 3rd, 5th, 7th, 30th, and 90th day after surgery. These examinations will include assessments of adverse drug events, cardiac ultrasound, chest X-ray, laboratory tests (blood routine examination, blood biochemistry, erythrocyte sedimentation rate, coagulation function, CK-MB, cardiac troponin I (cTnI), PCT, IL-6, CRP, myohemoglobin (MYO), type B natriuretic peptide (BNP), D-dimer, etc.) and clinical biomarkers (matrix metalloproteinase-9 (MMP-9), MMP-2, MMP-3, MMP-13, type III procollagen, etc.). CTA examination of the cervical, thoracic, and abdominal aorta artery will be performed before surgery and on the 30th and 90th days after surgery.

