## Discussion

This study presents the first randomized, double-blinded, and placebo-controlled trial conducted to evaluate the safety and efficacy of ketorolac in the treatment of aTAAD. The findings of this trial will serve as a valuable reference for the use of ketorolac in the treatment of aTAAD. If the hypothesis of this trial proves to be accurate, ketorolac treatment for aTAAD can be considered safe and potentially beneficial in reducing inflammatory biomarkers, such as IL-6, CRP, and PCT.

The guidelines state that ketorolac can increase hypertension and cause renal dysfunction, so patients with acute aortic syndrome should use it with caution [16]. However, the guidelines only mention aortic disease and do not specifically address the potential harm of ketorolac in aTAAD. There is also no clear literature support provided. Previous clinical studies have shown that ketorolac is safe for perioperative treatment of surgery [26], and it has also been found to be beneficial in the treatment of aTAAD [15]. Our preliminary basic experiments have confirmed the beneficial effects of ketorolac on animal aortic aneurysms, which align with the conclusions of published basic research papers [12, 27, 28]. From a clinical application perspective, patients in the ICU undergo strict monitoring of their blood pressure, urine output, etc. Active treatment methods can effectively control the hypertension and kidney damage that are concerning in the guidelines. Therefore, the use of ketorolac in the treatment of aTAAD remains a controversial issue.

We intend to reevaluate the safety and efficacy of ketorolac in the treatment of aTAAD. Our approach involves two main components: Firstly, we will conduct a randomized controlled trial. Secondly, we will collect aortic tissue samples from patients during surgery and perform a series of laboratory experiments to investigate the underlying mechanisms and pathways. By integrating both clinical trials and basic experiments, our study aims to offer scholars a solid reference framework and novel insights.

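### For repeatedly measured continuous secondary outcomes the article names only normality-gated two-sample tests, with no stated use of the pre-operative value, no repeated-measures model and no key time point

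*Protocol article*

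**What the plan says.** The rule is in Statistical methods for primary and secondary outcomes {20a}. Continuous variables are summarised as mean ± standard deviation. "The Kolmogorov–Smirnov test will assess normal distribution". Then: "If variables exhibit normal distribution, an independent sample *t*-test will be employed; otherwise, the Mann–Whitney *U* test will be utilized". The same section adds: "Double-tailed *p*-values and 95% confidence intervals will be reported, with statistical significance defined as *p* < 0.05". It mentions no baseline covariate, change score, summary measure, longitudinal model or principal visit.

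The data are richer than that rule.

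- Intervention description {11a} schedules "follow-up examinations before surgery and on the 1st, 3rd, 5th, 7th, 30th, and 90th day after surgery", covering routine blood tests among other assessments. CTA "will be performed before surgery and on the 30th and 90th days after surgery".
- The section on biological specimens {33} says that, for ELISA, "blood samples will be collected before surgery and at 1, 3, 5, and 7 days after surgery".
- Table 1 marks haematology, CTA and echocardiography in the enrolment column and again after surgery. Echocardiography is marked on days 3, 30 and 90.

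The Discussion says that, if the hypothesis proves right, ketorolac can be considered safe and "potentially beneficial in reducing inflammatory biomarkers, such as IL-6, CRP, and PCT". These three markers are all measured repeatedly.

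**The concern.** A two-sample test takes one number per patient. When a marker has one value before surgery and up to six after it, the analyst must still decide which number enters the test, and the article does not say. Three things are at stake.

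- **Precision.** A pre-operative value that predicts the later value removes noise from the treatment comparison. Leaving it out gives up precision that the collected data could supply.
- **Interpretation.** The t-test compares means and the Mann–Whitney test compares ranks. If the data choose between them, one marker or visit may be judged on means and the next on ranks. All are still summarised as mean ± SD, and no interval to accompany the rank test is named.
- **Selectivity.** With many markers, several visits, a 0.05 threshold and no key day, isolated significant biomarker results are easy to obtain. The Discussion's statement about inflammatory markers would rest on such results.

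**Working it through.** **The plan's own figure.** Sample size {14} takes composite event rates of 70% under placebo and 40% under ketorolac, with 53 per arm and over 90% (the article calls it confidence; power is evidently meant). With unpooled variance and two-sided alpha 0.05:

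n = (1.960 + 1.282)² × (0.7×0.3 + 0.4×0.6) / 0.3² = 52.5, so 53 per arm, with power 90.2%.

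The figure reproduces. (The pooled-variance version gives 56 per arm, and 88.5% power at 53.) Sixty per arm allows 1 − 53/60 = 11.7% loss. All of this concerns a binary composite, so the present point does not touch it. The article gives no figure for any continuous outcome.

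**Precision.** The article gives no baseline-to-follow-up correlation ρ and no expected biomarker effect. Assumed here: ρ = 0.3, 0.5 or 0.7, and an effect of 0.5 SD for illustration. Relative to the unadjusted post-operative comparison (variance 1), ANCOVA has variance f = 1 − ρ², and a change score has 2(1 − ρ) if the variance is the same before and after. The equivalent unadjusted sample is 53/f, and power = Φ(0.5 × √(53/2) / √f − 1.96).

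| ρ (assumed) | ANCOVA variance | Change-score variance | Equivalent n per arm | Power, post value only | Power, ANCOVA |
|---|---|---|---|---|---|
| 0.3 | 0.91 | 1.40 | 58 | 73% | 77% |
| 0.5 | 0.75 | 1.00 | 71 | 73% | 84% |
| 0.7 | 0.51 | 0.60 | 104 | 73% | 95% |

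The reduction is therefore 9%, 25% or 49%. At ρ = 0.1 or 0.2 it would be only 1% or 4%.

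**Number of tests.** Secondary endpoints names 19 routine blood markers:

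- four inflammatory (ESR, CRP, procalcitonin, SII);
- three coagulation;
- five liver;
- three renal;
- troponin, natriuretic peptide and two myocardial enzymes.

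It also names 12 ELISA analytes. If each were tested at each post-operative visit:

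19 × 6 + 12 × 4 = 114 + 48 = 162 tests; 162 × 0.05 = 8.1 expected false positives under no effect.

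This expectation does not require independence. For a single marker over six visits, the chance of at least one p < 0.05 is 1 − 0.95⁶ = 26.5% if visits are independent. In simulation (53 per arm, 20,000 runs) it is 24%, 20%, 17% or 11% for a between-visit correlation of 0.3, 0.5, 0.7 or 0.9.

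**The normality gate.** This was simulated under no effect at 53 per arm with 5,000 runs. The Kolmogorov–Smirnov test was applied to each arm at 5% with estimated mean and SD; the article does not specify this detail.

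| Distribution | Type I error | Runs sent to Mann–Whitney |
|---|---|---|
| Normal | 5.0% | 0.1% |
| Lognormal, σ = 0.5 | 5.8% | 24% |
| Lognormal, σ = 1 | 5.1% | 97% |

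Type I error hardly moves. The middle row shows the real cost: for a moderately skewed marker, the same distribution leads to a mean comparison in about three-quarters of samples and a rank comparison in the rest.

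**The case against.** The strongest reply is that the article does not say what enters the test. A reader might infer that it prescribes visit-by-visit testing and throws the baseline away, but neither is stated. The same tests could be applied to a change score, a peak or one chosen day, and an analysis plan that is not shown may say so. That stands, and it makes the count of 162 conditional. It does not remove the point: the article itself fixes the gate and the two-sample tests for all continuous variables, and even a change-score t-test is less precise than ANCOVA at every correlation tabulated.

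Other stronger readings also fail.

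- Chance baseline imbalance does not bias the unadjusted comparison. Randomisation protects it and its confidence interval already allows for chance imbalance. The loss is one of precision.
- The gate does not materially inflate type I error in the simulations. Its harm is to interpretation.
- The gain from adjustment may be small. No figure in the article supports any particular correlation between an emergency pre-operative value and one taken after major surgery.
- The biomarker sentence in the Discussion is conditional and cautious. It is not the trial's primary conclusion.

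A fair objection to the remedy also stands. Sample size {14} cites 25% in-hospital mortality, and a mixed model running to day 90 implicitly models values after death.

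**Conclusion.** The point holds for continuous secondary outcomes only. For outcomes measured before surgery and repeatedly afterwards, the article fixes a data-selected two-sample test and states no use of the baseline, no repeated-measures model and no key time point. A better method is available from data already being collected.

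The size of the gain is uncertain. The 9% to 49% cut in residual variance rests on assumed correlations of 0.3 to 0.7. The figure of about 8 false positives holds only if every named marker is tested at every scheduled visit. What needs no assumption is that the gate can change what is being compared from one marker or visit to another, and that a rank test does not match a mean ± SD summary. The primary endpoint and the 53 (60) per arm are unaffected. The change is worth making, but it does not decide the trial's main result.

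**What to change.** In Statistical methods for primary and secondary outcomes {20a}:

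1. For outcomes with a pre-dose value, replace the gated tests by a baseline-adjusted analysis. Use ANCOVA for a single time point, or a mixed model with treatment, day, treatment-by-day, baseline and baseline-by-day. Analyse skewed markers on the log scale. Report the adjusted difference or ratio with its 95% confidence interval.
2. Drop the Kolmogorov–Smirnov gate.
3. Name one day each for IL-6, CRP and procalcitonin, and label other markers and days exploratory. For IL-6, state which measurement is meant: it appears among the routine tests in Intervention description {11a} and among the ELISA analytes in Secondary endpoints.
4. Confirm that the baseline sample precedes the first study dose. That dose is itself given before surgery, and Table 1 does not list the ELISA sample separately.
5. State how deaths before a visit are handled.

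The cost is revised wording and a little more programming in R, which the article already names; no new data are needed. The price is a modelling assumption about values missing after death, which an early post-operative key day limits.

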## Assignment of interventions: allocation

### Sequence generation {16a}

This study employs a block-randomized treatment allocation strategy to minimize selective bias in treatment assignment. The trial utilizes a block randomization approach, facilitated by SAS 9.4 statistical software, with participants allocated in a 1:1 ratio to the ketorolac and placebo groups. Sequentially numbered random codes are generated based on the “Central Code Random Number Table.” The random number table is provided by qualified professionals. As recruitment is finishing, participants can only obtain a random code, without knowledge of the corresponding medication.

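### The primary composite is compared by a valid but unadjusted test, although plausible prognostic baseline values are collected before allocation; adjusting for a short, pre-named list would be a cheap gain in efficiency

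*Protocol article*

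**What the plan says.** Protocol article, Statistical methods for primary and secondary outcomes {20a}: categorical variables "will be expressed as percentages and analyzed using the chi-square test" or Fisher's exact test, two-sided, "with statistical significance defined as *p* < 0.05". The sentence is general and does not name the composite. However, the section covers primary outcomes, and the primary efficacy endpoint is an event composite sized on two proportions, so it falls under this rule. No adjusted model appears.

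Sequence generation {16a} describes blocks, "with participants allocated in a 1:1 ratio to the ketorolac and placebo groups", and names no stratification factor.

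Plans for assessment and collection of outcomes {18a} lists "Clinical data, including patient admission information, demographic data, laboratory blood examinations, and imaging examinations" as collected. Table 1 places hematology, CTA and echocardiography in the enrolment column, and Intervention description {11a} adds preoperative biochemistry.

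Sample size {14} assumes 70% events on control and 40% on ketorolac, and states that "when the sample size of the ketorolac group and the control group is 53 cases, this difference can be detected with over 90% confidence". The total is then raised to 60 per arm.

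**The concern.** Neither the randomisation as described nor the named test uses baseline risk. In a trial of this size, baseline values that predict the outcome can narrow the interval for the risk difference without one more patient. Age, preoperative creatinine or eGFR, ejection fraction and dissection extent are plausible candidates, and all can be had before the first injection.

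What is at stake is precision and power, not validity. The matter has some weight because, at the 53 evaluable patients per arm that the plan itself works with, the chi-square test falls slightly short of the power that the plan states.

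**Working it through.** **Inputs.** From Sample size {14}: event rates 0.70 and 0.40, 53 evaluable and 60 randomised per arm. From {20a}: two-sided 0.05, chi-square or Fisher. Not in the documents: how well the baseline values predict the composite. That is an assumption, taken over R² from 0 to 0.25 (c-statistic about 0.50 to 0.79).

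**1. The plan's own figure.** Reading its word confidence as power, the unpooled normal formula gives
n = (1.960 + 1.282)² × (0.70×0.30 + 0.40×0.60) / 0.30² = 10.507 × 0.45 / 0.09 = 52.54, so 53 per arm, with power 90.2%. The stated figure is reproduced. Allowing 10% loss, 53/0.9 = 58.9, rounded up to 60.

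**2. The test the plan names.** The Pearson chi-square uses the pooled rate 0.55 under the null:
- SE₀ = √(2×0.55×0.45/53) = 0.0966
- SE₁ = √(0.45/53) = 0.0921
- Power = Φ((0.30 − 1.960×0.0966)/0.0921) = Φ(1.20) = 88.5%

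Exact binomial enumeration:

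| Per arm | Chi-square | Fisher |
|---|---|---|
| 53 | 87.8% | 83.6% |
| 60 | 92.4% | 89.4% |

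Expected cell counts at 53 per arm are about 29 and 24 (53×0.55 and 53×0.45), so the chi-square test is the natural reading.

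**3. Effect of adjustment at 53 per arm.** Multiplying both variances in step 2 by (1 − R²):

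| Assumed R² | Power |
|---|---|
| 0 | 88.5% |
| 0.05 | 90.1% |
| 0.10 | 91.6% |
| 0.15 | 93.0% |
| 0.20 | 94.3% |
| 0.25 | 95.6% |

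Logistic-regression simulation with one or four normal covariates, Wald test, 6000 replicates, Monte Carlo error about 0.4 points:

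| Assumed c-statistic | Power |
|---|---|
| 0.50 | 87.7-87.8% |
| about 0.63 | 89.5% |
| about 0.70 | 91.3% |
| about 0.74 | 92.8-93.1% |
| about 0.79 | 94.1-94.4% |

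A separate simulation of the standardised risk difference with four covariates (3000 replicates) agrees. At 53 per arm, power rises from 88.3% to 91.0% (c = 0.69) and from 87.4% to 91.9% (c = 0.74). At 60 per arm it rises from 92.7% to 94.5% and from 92.5% to 95.0%.

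**4. Type I error.** The logistic Wald test rejected a true null in 4.6-5.7% of replicates, and the likelihood-ratio test reached 6.3% in one four-covariate setting. The standardised estimator gave 5.1-6.2%, against 4.3-5.7% for the crude test.

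A liberal test buys some power by itself. At a true level of 6.2% (critical value 1.866) the step 2 formula gives Φ((0.30 − 1.866×0.0966)/0.0921) = 90.3% with no covariates at all. The gain is still not merely that. With one covariate the Wald test rejected a true null in 4.6% (c about 0.70) and 4.7% (c about 0.79) of replicates, with power of 91.3% and 94.4%.

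These figures ignore the planned interim analysis. Patient deletion enters only through the choice of 53 rather than 60.

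**The case against.** The strongest reply is that nothing here is wrong. An unadjusted chi-square test after 1:1 randomisation controls type I error, and covariates are often settled in an analysis plan that is not shown. The first half stands in full. The second does not dispose of the point, because the article does state a primary method, and the proposal is to replace it with a more efficient one.

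Several stronger readings are tempting, and the documents do not support them:

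- *That strong predictors are being ignored.* The article shows only that the values are collected and gives no prognostic strength. Eligibility criteria {10} exclude age over 65, renal insufficiency, malperfusion, limb ischaemia, preoperative intubation and mechanical support, which narrows the spread of baseline risk.
- *That adjustment yields 91-92% power.* That holds only for an assumed R² of roughly 0.08-0.12. With uninformative covariates the gain is nil, although the loss is also negligible.
- *That adjustment is free.* Baseline values may be blank: {20c} leaves up to 10% of a patient's data empty, and dropping such patients could cancel much of the gain. The small-sample variance also needs care.
- *That the sample size is wrong.* The 53 per arm reproduces with the unpooled test, and a full 60 per arm already gives about 92% unadjusted.
- *That chance imbalance is a flaw.* For four independent binary factors at 60 per arm, each has a probability of about 0.09 (30% prevalence) or 0.12 (50%) of differing by 15 points or more. At least one then does so with probability 1 − 0.91⁴ = 0.31 to 1 − 0.88⁴ = 0.40. The factors and prevalences are assumed, and the crude test's error rate already allows for such differences.

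**Conclusion.** The point holds as an efficiency improvement of modest and uncertain size. The crude chi-square test is valid and has about 88% power at 53 evaluable per arm and about 92% at 60. At 53 per arm, adjustment would give about 88% with uninformative covariates, about 90% at modest strength, 91-93% at a c-statistic of about 0.70-0.74, and up to about 94-96% beyond that. At a full 60 per arm the gain is smaller, about two points in the settings simulated.

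All of this assumes the plan's 70% against 40%, and the prognostic strengths are assumptions with no source in the documents. The case for acting rests on an asymmetry: useless covariates cost almost no power, and useful ones recover the 90% that the plan aims for.

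**What to change.** In {20a}, name as the primary efficacy analysis a covariate-adjusted risk difference with its 95% interval. Fit a logistic regression on arm plus a short list of baseline covariates (for example age, preoperative creatinine or eGFR, ejection fraction and dissection extent on CTA), then standardise the predictions over all analysed patients under each arm. This keeps the marginal risk-difference scale of the sample-size assumption, which a conditional odds ratio would not.

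- Use a small-sample-corrected robust variance or a permutation test. Without one, type I error can run slightly above 5%, up to about 6%.
- Keep the list short: at 106 evaluable patients and a 55% overall rate there are about 48 non-events (106×0.45) for the model to use.
- Fill blank baseline values by a simple imputation that ignores arm, so that no patient is dropped for a missing covariate.
- Fix the covariates before any outcome by arm is seen at the interim. That analysis comes at 60 patients, and Trial status reports 55 included by 20 March 2024.
- Retain the chi-square test as the supportive analysis.

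The cost is a short amendment and a few lines of R, which the plan already uses. No new data collection is needed. The downside is that the covariate list must be fixed now, without figures in the documents to show how informative it will prove.
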